### Who will take informed consent? {26a}

The potential patients will receive complete and adequate information about the protocol, and they will have a reflection period of at least 7 days before the signature of the informed consent in the presence of the investigators. If patients are under legal guardianship, written agreement from their legal guardians should also be obtained.

### Additional consent provisions for collection and use of participant data and biological specimens {26b}

On the consent form, participants will be asked if they agree to use of their data should they choose to withdraw from the trial. Participants will also be asked for permission for the research team to share relevant data with people from the universities taking part in the research or from regulatory authorities, where relevant. This trial does not involve collecting biological specimens for storage.

### Interventions

#### Explanation for the choice of comparators {6b}

Patients will be randomized to receive a short ECT protocol or a long ECT protocol.

##### Short ECT protocol

The short ECT protocol is a standard protocol to treat URS patients, inspired by the continuation protocols commonly used in depression [8]. However, it is limited by a relatively high relapse rate. In this protocol, 20 sessions of ECT will be administered in 6 months with the following schedule: twice a week for 6 weeks and then once a week for 4 weeks. Afterwards, the patients will have ECT sessions every 3 weeks for 6 weeks and then each month for 2 months.

##### Long ECT protocol

Increasing the number of sessions, increasing the duration of treatment, and reducing the frequency more gradually could decrease the risk of relapse in URS patients.

In this long protocol, all the phases are doubled and could resemble a maintenance protocol used in depression [9]. In the long arm, 40 sessions of ECT will be administered in 12 months with the following schedule: twice a week for 12 weeks and then once a week for 8 weeks. Afterwards, the patients will have ECT sessions every 3 weeks for 12 weeks and then each month for 4 months.

### Intervention description {11a}

#### ECT equipment

For the two protocols (short and long), the main ECT devices which will be used are the THYMATRON System IV (SOMATICS, LLC, [name]) or the spECTrum 5000Q (MECTA Company/Micromed, [name]). ECT will be administered through bilaterally positioned electrodes on the temporal region. The stimulation dose will be determined by the titration method during the first ECT session [10].

The dose for therapeutic stimulation will be twice the seizure threshold. As recommended, this dose may be increased if the seizure does not meet the effectiveness criteria.

#### Anesthesia procedure

The patient should have an anesthesia assessment during the month prior to ECT onset. An interview with the anesthetist should also be conducted prior to each ECT session. The patient should not eat or drink anything for the 12 h leading up to each session, except for cases of premedication. The administered pharmacological agents are written down on the anesthesia sheet. Infusion therapy is provided. Blood pressure, heart rate, and blood saturation of oxygen will be monitored. An adapted emergency box with all drugs needed to control any cardiovascular effects will be at disposal and checked before each session.

Loss of consciousness is insured by the administration of one short-lasting hypnotic drug: etomidate (between 0.1 and 0.7 mg/kg). This dose should allow recovery within 5 to 10 min. Patient safety is guaranteed by the administration of a short-lived curare: suxamethonium chloride (between 0.8 and 1.2 mg/kg), a dose allowing both the decrease of the muscular contraction intensity and spontaneous breathing recovery within 3 or 5 min. The required doses are adapted to each patient by the anesthetist. During each ECT session, the anesthetist records cardiovascular parameters (heart rate and systolic and diastolic blood pressure). After the convulsive phase, breathing enriched with oxygen is insured by mask ventilation until spontaneous breathing recovery, after which the patients remain 1 h in the recovery room. Then, they are taken by ambulance back to their wards. Getting back to normal eating habits happens 1 h and a half to 2 h after recovery.

The medical team to be present during the ECT session is composed of the psychiatrist who is responsible for administering the electroshock, the anesthetist, and the nurse anesthetist.

#### Criteria for discontinuing or modifying allocated interventions {11b}

The patients stop participating in the study in the following cases:
Removal of the patient consent or the legal guardian agreement (in these cases, the collected data are not included in the data analysis)Patients refusing to continue the study, without removal of consent (patients’ data may be analyzed)Decision of the investigator: if the patient’s clinical condition worsens, significant adverse effects occur, wish of the patient to receive more ECT when he/she is assigned to the short arm, need to change the background drug treatment, impossibility for the patient to follow the established protocolDeath of the patient;Patients lost to follow-up (after unsuccessfully trying to contact the patient three times at 1-week intervals)

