#### Exit criteria

The patients are definitively excluded from the study in the following cases: removal of the patient’s consent or the legal guardian agreement (in these cases, the collected data are not included in the data analysis)Patients refusing to continue the study, without removal of the consent (in these cases, the collected data will be included in the data analysis)Decision of the investigator: worsened clinical condition, occurrence of significant adverse effects, need to change the background drug treatment, and impossibility for the patient to follow the established protocolDeath of the patient;Patient lost to follow-up (after unsuccessfully trying to contact the patient three times at 1-week intervals)

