### Plans to promote participant retention and complete follow-up {18b}

No specific strategy is planned to promote participant retention. However, resistant schizophrenic patients are mostly long-term hospitalized patients because of their serious illness. Being hospitalized can guarantee adherence to care. As far as possible, if the patient wishes to stop ECT sessions, it is recommended to proceed to the next follow-up visit in order to have the most concomitant data of the end of the ECT.

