### Methods in analysis to handle protocol non-adherence and any statistical methods to handle missing data {20c}

Comparison of the two treatment arms will be based on the intent-to-treat principle. The maximum bias hypothesis shall be considered for non-assessed patients 3 months after the end of the treatment (patients lost to follow-up). Those patients, if in the group with the most favorable evolution, shall be considered as having not responded. On the contrary, those patients, if in the group with the most unfavorable evolution, shall be considered as responding to treatment. The aim is to reduce the gap between both to a minimum. By doing so, a robust conclusion is expected. Then, several sensitivity analyses shall be carried out: one analysis excluding patients lost to follow-up (per-protocol analysis) and another imputing the missing data by the last observed value (“last observation carried forward”).

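### Clinical worsening, a drug change or (short arm only) a wish for more ECT ends study participation, so the primary PANSS is lost for outcome-related reasons in an intent-to-treat trial

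*Protocol article*

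**What the plan says.** The section on criteria for discontinuing or modifying allocated interventions {11b} opens its list with "The patients stop participating in the study in the following cases". Among the investigator-decision reasons are clinical worsening, a need to change background drugs and "wish of the patient to receive more ECT when he/she is assigned to the short arm". The Exit criteria section gives a parallel list that makes the exclusion definitive, including "Decision of the investigator: worsened clinical condition, occurrence of significant adverse effects, need to change the background drug treatment", but leaves out the short-arm reason. Both lists give loss to follow-up as a separate item.

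The primary outcome is PANSS response three months after treatment ends: month 9 in the short arm and month 15 in the long arm (Main outcome). On analysis, {20c} states: "Comparison of the two treatment arms will be based on the intent-to-treat principle". For missing outcomes it states: "The maximum bias hypothesis shall be considered for non-assessed patients 3 months after the end of the treatment (patients lost to follow-up"; the last words stand in a parenthesis. Under this rule a missing patient in the better arm is a non-responder, and for the worse arm: "On the contrary, those patients, if in the group with the most unfavorable evolution, shall be considered as responding to treatment". The sensitivity analyses exclude patients lost to follow-up and, in "another imputing the missing data by the last observed value", use LOCF.

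On retention, {18b} plans no specific strategy and says only that "if the patient wishes to stop ECT sessions, it is recommended to proceed to the next follow-up visit".

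**The concern.** The exit rules merge two decisions: stopping or changing the allocated ECT, and ending outcome assessment. Intent to treat needs the second to continue after the first. Here the listed reasons are markers of poor response or relapse, and one of them can arise in the short arm only. The primary PANSS then goes missing for reasons tied to its own value and unevenly by arm. Section {17a} adds that patients and care providers know the allocation, so these exits are discretionary and unblinded.

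This bears on the main question. The Sample size section derives the short-arm rate from a 62.5% relapse rate after ECT stops. A patient who relapses may worsen, need other drugs or ask for more ECT, and each of these is an exit reason. A later analysis plan cannot recover a PANSS that was never collected.

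**Working it through.** **Coverage by the existing safeguards**

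- The recommendation in {18b} concerns patients who wish to stop ECT. It does not reach a short-arm patient who wants more, and the next visit need not be the primary visit.
- The maximum bias rule in {20c} refers to non-assessed patients, then names in parenthesis only those lost to follow-up, which the exit lists treat as a separate reason. Reading 1: the rule covers the exits. Reading 2: it does not, and no primary rule is stated for them.
- LOCF would code a worsening recorded at a visit as non-response. The schedule has no visit between months 6 and 9, so a short-arm exit in that interval carries forward the end-of-ECT score. LOCF is in any case a sensitivity analysis.

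**The plan's own figure**

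Inputs from Sample size {14}: p1 = 0.6179 (long), p2 = 0.2325 (short), alpha 0.05 (taken as two-sided), power 0.80, drop-out 20%. With pooled variance and no continuity correction, and mean rate 0.4252:

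n = [1.960 × √(2 × 0.4252 × 0.5748) + 0.842 × √(0.6179 × 0.3821 + 0.2325 × 0.7675)]² / 0.3854²

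= (1.370 + 0.542)² / 0.1485 ≈ 24.6, so 25 per arm. Then 25 / 0.80 = 31.25, so 32 per arm and 64 in total. The stated size is reproduced.

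**Power with exits**

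Test: Pearson chi-square without correction, two-sided 5%, 32 per arm. Exits are placed in the short arm only, at a fraction e of that arm. The protocol gives no exit rate by reason, so e is an assumption. With all outcomes observed, power is 0.906.

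Reading 1, with the long arm doing better, leavers counted as responders:

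- All leavers true non-responders: short-arm rate = 0.2325 + e.
- Half of leavers true responders: short-arm rate = 0.2325 + e/2.

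Reading 2, leavers left out (assumed handling), all true non-responders: short-arm rate = 0.2325 / (1 − e).

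| Scenario | e | Short-arm rate | Power |
|---|---|---|---|
| Reading 1, all non-responders | 5% | 28.25% | 0.81 |
| Reading 1, all non-responders | 10% | 33.25% | 0.67 |
| Reading 1, half responders | 5% | 25.75% | 0.86 |
| Reading 1, half responders | 10% | 28.25% | 0.81 |
| Reading 2 | 5% | 24.5% | 0.87 |
| Reading 2 | 10% | 25.8% | 0.83 |

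Under reading 1 with all leavers non-responders, equal exits in the long arm change nothing, because those patients are already non-responders and stay so: 0.81 at 5% and 0.67 at 10%. As an extreme, if 20% of the short arm (the whole drop-out allowance) left in this way, the short-arm rate would be 43.25% and power 0.35.

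**Power if leavers are followed**

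Suppose leavers would otherwise not respond, receive extra ECT and then respond at 61.79%. Short-arm rate = 0.2325 + e × 0.6179. At 5% this is 26.3% with power 0.85. At 10% it is 29.4% with power 0.78, against 0.67 under reading 1.

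**Coding every such exit as non-response**

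Take a true rate of 61.79% in both arms and let short-arm patients who would have responded exit. The short-arm rate becomes 56.79% at 5% and 51.79% at 10%. The two-sided rejection rate rises from 5.4% with full data to 7.6% and 14.1%. That coding should not be the primary rule.

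**The case against.** The strongest reply is that {20c} already handles these patients. Its operative term is non-assessed, the parenthesis can be read as a loose gloss, and the same phrase recurs in the exclusion analysis, where it most naturally means everyone without the primary value. On that reading all randomised patients stay in the comparison and the rule works against the long arm. This stands in part: reading 1 is the more natural one, and under it there is no false claim for the long arm. It does not restore the lost values, and it counts a short-arm patient who worsened as a responder.

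It is also fair that the size rests on assumed exit rates. At 5% exits power stays at or above 80% in every scenario shown. At 10% it falls clearly below target only under reading 1 with all or most leavers true non-responders, and some patients may ask for more ECT because it helped. Exit is a decision and not automatic, and a short-arm exit after month 9 costs no primary value. All of this stands and limits the severity.

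Finally, a PANSS observed after extra ECT credits the short arm with that treatment's effect. This is a real cost, but it follows from the intent-to-treat principle the protocol has chosen.

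**Conclusion.** The concern holds and should be fixed. As written, the exit rules lose the primary PANSS for reasons related to outcome and, for one reason, confined to the short arm, and it is unclear which primary rule then applies. The consequence is a distorted short-arm rate and a loss of power from 91% to between 67% and 83% at 10% short-arm exits, or to between 81% and 87% at 5%, depending on the reading and on how many leavers are true responders. The calculations assume 32 per arm, the planned response rates and exits in the short arm only. If the maximum bias rule applies, a false claim for the long arm is not the risk.

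**What to change.** - In Exit criteria and {11b}, separate stopping or departing from the allocated ECT from leaving follow-up. Patients who worsen, change drugs or want more ECT keep their scheduled assessments to month 9 (short) or month 15 (long), unless they withdraw consent or refuse to continue. Align the two lists. Clinical stopping decisions do not change.
- Use the PANSS observed at the primary visit in the intent-to-treat analysis.
- In {20c}, state that the maximum bias rule applies to any patient without a primary-visit PANSS, whatever the reason.
- Confine coding of exit for worsening or for more ECT as non-response to a sensitivity analysis, given the type I error shown above.

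The cost is protocol wording and a few visits that are already scheduled. The downside is that some primary values will reflect extra ECT or changed drugs, which can narrow the difference between arms.

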According to a recent meta-analysis of 18 randomized controlled trials comprising 1769 patients, ECT augmentation of clozapine had superior efficacy to clozapine as a monotherapy, was safe and relatively well tolerated by clozapine-resistant patients [4]. However, 17 of the 18 studies included in the meta-analysis were in Chinese, not allowing us to judge their scientific quality. Only one methodologically sound study was published in English by Petrides et al. [5]. In this prospective randomized study, 39 patients with clozapine-resistant schizophrenia were assigned either in the “ECT plus clozapine” group (*n* = 20) or in the “clozapine” group (*n* = 19). In the intent-to-treat analysis, ten of the 20 patients (50%) in the ECT augmentation group but none of the patients (0%) in the clozapine group met the response criterion. The response was defined as a 40% reduction in symptoms based on the psychotic symptom subscale of the Brief Psychiatric Rating Scale (BPRS), a Clinical Global Impressions (CGI)-severity rating of mild or less (less than 3), and a CGI improvement rating of much improved (less than or equal to 2). Augmentation of clozapine with ECT is therefore an extremely promising therapeutic strategy for patients suffering from URS, but there is a lack of randomized controlled trials investigating important methodological aspects such as the optimal number and frequency of sessions as well as the need for maintenance ECT. For example, it seems that a larger number of ECT sessions is required in patients with TRS than in depression [6], but without real experimental evidence. In fact, the duration of most studies about ECT in URS patients is relatively short (between 4 and 6 months), and a high relapse rate was reported in the weeks to months after ECT cessation [7]. In order to decrease the risk of relapse, some experts empirically recommended ECT protocols with a duration ranging from 6 to 12 months. To our knowledge, advantages and disadvantages of a short versus a long treatment protocol have never been investigated. In this context, we designed a prospective randomized controlled trial in order to compare the effects of two different duration protocols of combining ECT with clozapine in URS patients.

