### Outcomes {12}

#### Main outcome

The main outcome is the response rate assessed by the Positive and Negative Symptoms Scale (PANSS) 3 months after the end of the treatment in patients following the long protocol (i.e., at 15 months) compared to those following the short protocol (i.e., at 9 months), the response being defined as a 30% reduction on the PANSS [12].

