#### Secondary outcomes

The secondary outcomes are as follows:
The response rate assessed by the Brief Psychiatric Rating Scale-18 items (BPRS-18) 3 months after the end of the treatment in patients following the long protocol compared to those following the short protocol (the response being defined as a reduction of 30% on the BPRS).The response rates assessed by the PANSS and the BPRS at different times (2, 4, 6, and 12 months) between both groups.The Hamilton Rating Scale-21 items (HAMD-21) score, the Young Mania Rating Scale (YMRS) score, the Modified Overt Aggression Scale (MOAS) score, the Clinical Global Impression (CGI) score, and the Global Assessment Functioning (GAF) score at baseline and at 2, 4, 6, 9, 12, and 15 months. Changes from baseline will be compared between both groups.The Mini-Mental Status Examination (MMSE), the Subjective Scale to Investigate Cognition in Schizophrenia (SSTICS) [13], the RL/RI-16 test assessing verbal memory [14], the Doors test assessing visual memory [15], the D2 Attention Test [16], and the Copy of the Rey-Osterrieth Complex figure test for the evaluation of visuospatial constructional ability [17] at baseline and at 6 and 15 months. Changes between baseline and 6 months and between baseline and 15 months will be compared between the groups.Plasma clozapine concentration measured at baseline and at 2, 4, 6, 9, 12, and 15 months in order to check patient compliance.

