### Sample size {14}

The aim of this trial is to compare the response rates between short and long ECT protocols. According to the meta-analysis of Lally et al. [7], the proportion of patients with treatment-resistant schizophrenia that responds to ECT augmentation of clozapine was 61.79% (Table 1: 55/89 cases). However, the relapse following ECT cessation is very high: the relapse rate has been estimated at 62.5% by Kho et al. [18]. On the other hand, Braga et al. [19] suggested that ECT were effective as a continuation strategy to prevent relapse after an acute course of ECT. During the 6-month maintenance period, no patient presented with clinically worsening symptoms. From this literature data, we postulate that the responder rates would be 61.79% in the long ECT protocol and 23.25% in the short ECT protocol (62% × (1 − 0.625) = 23.25%). Assuming an alpha risk of 0.05 and a power of 0.80, we estimated the need to include 25 patients per group. To overcome an estimated 20% drop-out, the required number of patients increased to 32 patients per group. As a result, the total number of participants required for the study is 64 patients.

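### An exit ground that exists only for the short arm (wishing more ECT) can lose the month-9 primary PANSS in that arm and pull the comparison toward the null

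*Protocol article*

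**What the plan says.** The protocol article has two lists of reasons for leaving the study.

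- Criteria for discontinuing or modifying allocated interventions {11b} states when patients cease to take part in the study. Its investigator-decision item includes the "wish of the patient to receive more ECT when he/she is assigned to the short arm".
- Exit criteria gives the same item as "worsened clinical condition, occurrence of significant adverse effects, need to change the background drug treatment, and impossibility for the patient" to follow the protocol. A wish for more ECT is not in it. Neither list has a counterpart for the long arm.

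The primary outcome is PANSS response three months after treatment ends, at month 9 in the short arm and month 15 in the long arm (Main outcome). The protocol expects relapse in that interval. Background {6a} notes that "a high relapse rate was reported in the weeks to months after ECT cessation", and Sample size {14} says "the relapse following ECT cessation is very high" and puts the rate at 62.5%.

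Section {20c} adopts intent-to-treat and a maximum-bias rule for patients not assessed at the primary visit: "those patients, if in the group with the most unfavorable evolution, shall be considered as responding to treatment". In the better-performing group they count as non-responders. The rule's parenthesis names only patients lost to follow-up, so it is unclear whether withdrawn patients are covered. Section {18b} gives retention advice for one case only: "if the patient wishes to stop ECT sessions, it is recommended to proceed to the next follow-up visit".

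**The concern.** The clause ends participation, not just allocated treatment, and it can act in one randomised arm only. A short-arm patient who asks for more ECT before month 9 has plausibly relapsed or never responded, and that is what the primary outcome measures. An exit on that request therefore makes missingness depend on outcome, in one arm, by rule. The advice in {18b} does not secure the PANSS, because it addresses a patient who wants to stop ECT, not one who wants more.

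If {20c} covers withdrawn patients and the short arm is doing worse, each such patient is scored as a short-arm responder. If they are dropped instead, the short-arm denominator loses non-responders and its rate still rises, though less. On either route a real advantage of the long protocol becomes harder to detect.

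**Working it through.** **Inputs** (Sample size {14}): response 61.79% long and 23.25% short, alpha 0.05, power 0.80, 25 per group, 32 after a 20% drop-out allowance. A two-sided test is assumed.

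**The plan's figure.** The pooled-variance formula, with mean rate (0.6179 + 0.2325)/2 = 0.4252, is

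n = [1.96·√(2·0.4252·0.5748) + 0.8416·√(0.6179·0.3821 + 0.2325·0.7675)]² / 0.3854² = 24.6, so 25. Then 25/0.8 = 31.25, so 32. Both reproduce.

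**Short-arm make-up implied by the plan.** Of 62% initial responders, 62% × 0.375 = 23.25% stay responders (7.4 of 32) and 62% × 0.625 = 38.75% relapse (12.4 of 32). The other 38% never respond (12.2 of 32).

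**Method.** Exact enumeration of the uncorrected Pearson chi-square, two-sided 5%, 32 per arm. Nobody is missing except the short-arm leavers. Under maximum bias, leavers count as responders when the short arm's observed rate is the lower one, otherwise as non-responders. The shares leaving are assumed; the protocol gives none.

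**Apparent short-arm rate when a share q of relapsers leaves**

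- Maximum bias: 23.25 + 38.75·q, which is 27.1% (q = 10%) or 32.9% (q = 25%). The difference shrinks from 38.5 points to 34.7 or 28.9.
- Exclusion: 23.25/(1 − 0.3875·q), which is 24.2% or 25.7%.

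**Power** (90.6% with no exits)

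| Who leaves before month 9 | Patients | Maximum bias | Exclusion |
|---|---|---|---|
| 10% of relapsers | 1.2 | 83.3% | 87.4% |
| 25% of relapsers | 3.1 | 67.8% | 82.8% |
| 10% of never-responders | 1.2 | 83.5% | 87.5% |
| 25% of never-responders | 3.0 | 68.4% | 82.9% |

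Per patient, an expected 1, 2 or 3 non-responders lost under maximum bias gives 84.9%, 77.6% or 68.8%.

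**Planned LOCF sensitivity analysis.** It scores a never-responder correctly (90.6%) but carries a month-6 response forward for a relapser (83.3% or 67.8%).

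**Attribution.** If half of the departing relapsers would have left on another ground anyway, the clause's own effect is the fall from 87.3% to 83.3% (q = 10%) or from 81.1% to 67.8% (q = 25%). If all would have left anyway, it is nil.

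**Dependence on who leaves.** If the leavers are sustained responders, maximum bias and LOCF are unaffected (90.6%). Exclusion then moves toward the long arm (95.4% if 25% of them leave).

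**No true difference.** With both arms at 23.25% and 10% or 25% of relapsers leaving, the chance of a significant result favouring the long arm under maximum bias is 1.1% or 0.3%, against 2.6% with no exits.

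**The case against.** *Other grounds already reach these patients.* Worsening, inability to follow the protocol and refusal to continue appear in both lists and apply to both arms. A relapser fits the first. A patient who is no worse but insists on unscheduled ECT fits the second and perhaps the third. The clause may only name an example of what is already allowed. This stands, so every loss above is an upper bound for the clause, and deleting the words alone might change nothing.

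*Most of the exposure comes too late to matter.* The short arm's ECT-free follow-up runs from month 6 to month 15, and six of those nine months follow the primary visit. This also stands. Later exits cost short-arm patients only in secondary comparisons, such as "The response rates assessed by the PANSS and the BPRS at different times (2, 4, 6, and 12 months) between both groups" at its month-12 point.

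*The large losses come from {20c}, which is conservative on purpose.* In part. Under exclusion, power stays above 80% in every scenario shown. But a rule that guards against missing data is no reason to generate missing data in one arm, and the 20% drop-out allowance restores numbers without correcting non-responders scored as responders.

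*Stronger readings.* A reader might infer that the clause could manufacture a false advantage for the long arm. The primary analysis under maximum bias does not allow that, as the no-difference figures show. A reader might also infer that the clause certainly removes non-worsening patients who would otherwise have stayed, but the shared grounds rule out that certainty. Nor is there support for an offsetting bias from the long arm, since no ECT is scheduled for it in months 12 to 15.

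**Conclusion.** The point holds in a limited form. The two exit lists disagree, and the extra ground acts in one arm only, ends participation and can remove the primary PANSS for an outcome-related reason. If the leavers are mainly relapsers or never-responders, the comparison is pulled toward the null. The pull is strong under maximum bias (a loss of up to 7.3 or 22.8 points of power if 10% or 25% of relapsers leave, from 90.6 − 83.3 and 90.6 − 67.8). It is mild under exclusion (3.2 or 7.8 points).

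These sizes rest on assumed exit shares, the plan's own response and relapse rates, no other missing data and, for the larger pair, {20c} covering withdrawn patients. They credit every such exit to the clause, whose own share could be nil. The change is worth making because it is cheap and fits the intent-to-treat principle, not because a large loss has been shown.

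**What to change.** In {11b}, make a wish for more ECT, in either arm, a reason to stop the allocated schedule only and not the study. State that such a patient is not withdrawn under the inability-to-follow-the-protocol ground. Align Exit criteria with this.

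Keep the patient in follow-up. Take the PANSS at the arm's primary visit (month 9 short, month 15 long), or just before the first extra ECT if that comes earlier, and record the date of extra ECT. Whether and when to give it remains a clinical decision.

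Where extra ECT precedes the primary visit, use the pre-ECT PANSS in the primary analysis. Add two sensitivity analyses: the PANSS observed at the primary visit regardless of extra ECT, and extra ECT before that visit counted as non-response in both arms.

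The score after re-treatment should not be primary. If all departing relapsers were re-treated and 62% responded again, the short-arm rate would be 23.25 + 38.75·q·0.62, which is 25.7% or 29.3%. Power would be 86.4% or 78.2%, below exclusion (87.4% or 82.8%), and the short arm would be credited with ECT beyond its 20 sessions. If the pre-ECT PANSS shows these patients as non-responders, the clause's own loss is recovered in full. Exits for worsening would remain.

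Costs: revised wording, one eCRF date field, two extra analyses, an unscheduled PANSS that may hint at the arm to the blinded rater, and some primary scores taken earlier than the nominal visit.
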